**Figure 1 F1:**
[figure not shown]
Flow chart of the study.

### The intervention

2.5

#### Underpinnings of the intervention

2.5.1

Antibiotics prescribing is a multifactorial process. We have chosen to follow the Predisposing, Reinforcing, and Enabling Constructs in Educational Diagnosis and Evaluation (PRECEDE) phases from the PRECEDE-PROCEED^[26]^ model as the theoretical basis to design the intervention. As part of the PRECEDE phases, we carried out the various diagnoses and evaluations required by this model which stands for Predisposing, Reinforcing, and Enabling Constructs in Educational/ environmental Diagnosis and Evaluation.^[26]^ An unpublished ethnographic study conducted by our research team found that nurses’ communication skills were low, despite their essential role in describing symptoms to physicians by telephone, most often during episodes of suspected UTI. This nurse–prescriber communication in the event of antibiotic prescriptions for UTI is therefore essential because occurring in an environment where there are no doctors on site. This study also highlighted the difficulty nurses have in assessing suspected UTIs in nursing homes due to nonspecific clinical symptoms. Another conclusion of this study is the growing need for nurses to strengthen their knowledge of antibiotic therapy. Thus, the observations of our study on nurses’ communication and clinical judgment are in line with the national roadmap^[14]^ on antibiotics in France. Therefore, the current intervention will focus on nurses’ knowledge as a predisposing factor. Additionally, to assist nurses in their clinical judgment and reasoning, and in their telephone interaction with prescribers, we plan to provide nurses with a decision support diagram and a communication tool. This is the enabling factors of the intervention. Finally, the distribution of posters and pamphlets during visits to nursing homes to meet participants and the organization of a competition targeting the interventional group will be the reinforcing factor. This component aims to support the nurses’ adherence to the intervention, and also the sustainability of the intervention.

#### Interventional group

2.5.2

An interventional group based on 20 nursing homes will benefit a multimodal blended-learning intervention for 1 year. This intervention will include 4 main components, and also 2 implementation modalities. These components will include: awareness and knowledge reinforcement; improvement of communication skills; support for clinical judgment via the use of a decision aid diagram; and improvement of participants’ involvement and the sustainability of the intervention via the organization of a competition. The first implementation modality will take place in the nursing homes with face-to-face tutoring, while the other step will be performed online by self-training (Fig. 2).

**Figure 2 F2:**
[figure not shown]
Overview of the intervention.

At the beginning of the intervention period, investigators will visit each nursing home to meet with the nurses for a 30 minutes face-to-face meeting, to thoroughly describe and explain the intervention. During this meeting, they will also provide intervention tools including web links to access self-training, posters to raise awareness, and the paper version of a diagram. This diagram is a decision aid that first step is a suspicion of UTI by a nurse. Then, she/he will investigate additional symptoms to confirm this first suspicion. The other steps of the diagram include the investigation of the living environment and clinical context of the residents. Finally, after assessing vital signs, nurses will perform a monitoring and decide to call off-site physicians by phone.

The diagram combined to the SBAR tool (Situation, Background, Assessment, and Recommendation) is intended to help nurses analyse suspected UTI and improve phone discussions with off-site prescribers. SBAR is an easy-to-remember technique that allows consistent and structured communication between members of the healthcare team during a critical situation.^[27]^ As part of the follow-up, the first investigator of the paper will return to these institutions every 2 months to renew the posters and reminders, and discuss any problems that participants may have encountered during the online self-training.

For nurses, the internet-based training will consist of consolidating the interprofessional communication with prescribers, communication with residents and relatives, and reinforcing their knowledge. The different topics of this training will cover antibiotics, asymptomatic bacteria, and UTIs described in the PowerPoint presentations, and also a 5-minute video. The diagram described above will be 1 of these online tools. Each training topic on antibiotics, UTI, or resistance will be followed by an online self-evaluation. During this step, video files displaying nurses’ communication situations with physicians and residents or relatives in a UTI episode will be available as basis of the exercises. The marketing and communication department of the national insurance fund will provide technical assistance and support for the recording of these videos.

The last component of the intervention is the organization of a competition. This competition will consist of asking participants, including prescribers and nurses, to design and propose tools such as posters, videos, and slogans aiming at raising awareness on the use of antibiotics, among health professionals in nursing homes.

#### Follow-up of the interventional group

2.5.3

A lead nurse will be designated as a spokesperson in each interventional nursing home. The research team will follow this group by phone and by visiting the nursing homes regularly during the first 6 months of the intervention period. He will make 1 visit per nursing home every 2 months during the first follow-up period. The last 6 months of follow-up will be done by phone. During the intervention period, 1 member of the research team will call the lead nurses by phone every month to discuss any problems encountered during the online courses, and discuss potential tools or suggestions.

#### Control group

2.5.4

No intervention is planned for this group, and usual nurses’ practices will take place in these nursing homes.

### Outcomes

2.6

The main outcome is the reduction in the relative frequency of antibiotic prescriptions for UTI compared with all systemic route prescriptions of antibiotics.

This is defined as the ratio between antibiotics prescriptions for UTI (numerator) and antibiotics prescriptions for any reason (denominator). In this study, a prescription is defined as an order containing at least 1 systemic route antibiotic.

Secondary outcomes are overall antibiotic therapy prescriptions and antibiotics consumption expressed in daily defined dose (DDD) per 1000 resident-days. In addition, a medico-economic analysis is planned.

### Data collection and management and monitoring

2.7

Many data are expected (Table 2). Data sources will be 3-fold that are the Caisse National d’Assurance Maladie (CNAM) (French National Health Insurance Fund), the included nursing homes, and the webmaster. The CNAM, which has agreed to carry out these data survey, will provide researchers with global antibiotics prescriptions and the antibiotics consumption in DDD month to month. Data provided by the CNAM will also help cost analysis. Included nursing homes will provide reasons for the antibiotics prescriptions when an antibiotic prescription will be identified in the CNAM database. These nursing homes will also provide once characteristics of their facilities, staff, and residents, and month to month overall mortality. The information related to the use of the intervention website will be collected from this website by the researchers and the webmaster. They will collect: internet connexion time, self-training score per nursing homes, and time devoted by investigators to visit nursing homes during the intervention period.

**Table 2 T2:**
[figure not shown]
Outcomes expected.

For healthcare staff and residents, data will be collected with nursing home managers or coordination teams (nurses or doctors) during a specific appointment or the first visit. The third author will collect the number of urinalyses performed per nursing home from pharmacies that deliver drugs to nursing homes.

Data management and monitoring will be carried out by a private clinical research team. To ensure quality of data, the researchers have restricted the number of variables to those most relevant according to existing literature. Many numerical and logical controls like possible values for each variable and consistency of information about the same nursing home will be used to ensure data reliability in SAS 9.3.

### Statistical analysis

2.8

#### Missing data

2.8.1

Above 5% of missing data, investigators will perform multiple imputations according to the most likely mechanism.

#### Effect analysis

2.8.2

The main analysis will be performed in intent to treat, and a per-protocol analysis will also be carried out using SAS version 9.3 software with a 5% significance threshold. A mixed model which is the appropriate method in cluster study will be used to assess the impact of the intervention. No interim or subgroup analysis is planned in this study. A Poisson regression with random effects will be carried out to assess the impact of the intervention using secondary endpoints which are the total number of antibiotics per arm and mixed model for the antibiotics consumption expressed in DDD consumed during the year of follow-up of the interventional group. All models will consider the potential confounding factors such as average number of beds, average number of physicians, and average number of comorbidities.

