**Analysis::**

The main outcome is the reduction of the relative frequency of antibiotics prescription for UTIs in the interventional group.

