### Sample size

2.4

According to the Enquête nationale de prévalence des infections associées aux soins et des traitements antibiotiques en EHPAD 2016 national survey,^[4]^ the prevalence of antibiotic treatment for UTI was 33.3% in all prescribed systemic antibiotics. In addition, a resident will receive at least 1 prescription of antibiotic on average over a year.^[23]^

In our study, we assume that antibiotics for UTI will represent 30% of antibiotics prescriptions for 1 year, and that this percentage will not change in the control group after the intervention. We expect a 20% reduction after 1 year of intervention based on previous data on this issue^[24,25]^ in the intervention group. In a simple randomization, with a power of 80% and an alpha risk of 5%, 124 prescriptions of antibiotics per arm for UTI for a total of 414 prescriptions would be required to show this percentage of decrease in prescriptions for UTI. However, given the clustered design of our study, we must apply an inflation to this value. Additionally, we expect an average of size of 60 residents per nursing home and an intraclass coefficient of 0.05 for an inflation value of 3.95. Accordingly, 15 clusters or nursing homes per arm are required in this study. To anticipate withdrawals of consent, 40 clusters will be included, namely 20 nursing homes in the interventional group and 20 in the control group (Fig. 1).

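### The main outcome is worded as a reduction, yet no model names the homes' earlier prescribing; a baseline-adjusted between-arm comparison would add precision at little cost

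*Protocol article*

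**What the plan says.** The abstract states: "The main outcome is the reduction of the relative frequency of antibiotics prescription for UTIs in the interventional group". Section 2.6 repeats the idea without naming an arm: "The main outcome is the reduction in the relative frequency of antibiotic prescriptions for UTI compared with all systemic route prescriptions of antibiotics". It then defines the measure as UTI prescriptions divided by systemic antibiotic prescriptions for any reason. That is a level, with no before-and-after term.

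The sample size in section 2.4 is reasoned over time. It says "we assume that antibiotics for UTI will represent 30% of antibiotics prescriptions for 1 year", assumes that "this percentage will not change in the control group after the intervention", and adds: "We expect a 20% reduction after 1 year of intervention".

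Section 2.8.2 specifies a mixed model for the main outcome, a random-effects Poisson regression for the total number of antibiotics and a mixed model for DDD. The DDD model is tied to the follow-up year. On covariates it says only: "All models will consider the potential confounding factors such as average number of beds, average number of physicians, and average number of comorbidities".

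Under section 2.7 the national insurer "will provide researchers with global antibiotics prescriptions and the antibiotics consumption in DDD month to month". The calendar window is not given. The homes supply the reason for each prescription found in the insurer's data, and no pre-intervention period is mentioned for those reasons.

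**The concern.** A reduction needs a reference. Two randomised readings are open: lower than control during follow-up, or a larger fall from baseline than control. They call for different data and models and differ in precision. The outcome wording and the sample-size reasoning lean towards change over time, while the ratio and the models describe follow-up only. If this is left open, the choice could be made after the data are seen.

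Precision is also at stake. Only 40 homes are randomised, and the calculation requires 30. Section 2.3 describes no stratification or matching on prescribing; its only constraint is the 10 km rule. Chance differences between arms in prior prescribing are therefore likely to matter. Beds, physicians and comorbidities describe the facility and its residents, not how the home prescribed before. A home's own earlier prescribing would be expected to carry more information about its later prescribing, although the documents give no correlation to show how much.

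**Working it through.** **Inputs from section 2.4.** UTI share 30%; 20% reduction; power 80%; alpha 5% (taken as two-sided); 60 residents per home; ICC 0.05; 15 homes per arm required, 20 included. At least one prescription per resident-year gives about m = 60 prescriptions per home-year, which is an inference.

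**The plan's own figures.** The design effect reproduces: 1 + (60 − 1) × 0.05 = 3.95. The stated 124 UTI prescriptions per arm and 414 prescriptions in total do not reproduce as worded:
- 30% versus 24% (relative reduction): [1.96√(2 × 0.27 × 0.73) + 0.842√(0.30 × 0.70 + 0.24 × 0.76)]² / 0.06² gives 859 per arm.
- 30% versus 10% (absolute reduction): the same formula gives 62 per arm, or 124 for both arms together, and 124/0.30 = 413.3.

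That is a separate sample-size matter. Here it means only that the starting power depends on which effect is meant.

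**Power without baseline, 30% versus 24%.** Effective prescriptions per arm = homes × 60 / 3.95.
- 20 homes: 1200/3.95 = 303.8. SE under the null = √(2 × 0.27 × 0.73/303.8) = 0.0360; under the alternative = √(0.3924/303.8) = 0.0359. Power = Φ[(0.06 − 1.96 × 0.0360)/0.0359] = 38%.
- 15 homes: 900/3.95 = 227.8; power 30%.
- For 80% power: 859 × 3.95/60 = 56.6, so 57 homes per arm.

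**Effect of a baseline covariate.** The reliability of a home's yearly share is m × ICC / design effect = 60 × 0.05/3.95 = 0.76. The correlation between a home's baseline and follow-up shares is r = 0.76 × CAC, where CAC is the cluster autocorrelation. The documents give no CAC, so 0.5 to 0.9 is an assumption. Adjustment for baseline multiplies the variance by 1 − r².

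| CAC | r | 1 − r² | Effective n per arm (20 homes) | Power | Homes per arm for 80% |
|---|---|---|---|---|---|
| none | – | 1 | 303.8 | 38% | 57 |
| 0.5 | 0.38 | 0.856 | 355.0 | 44% | 49 |
| 0.7 | 0.53 | 0.717 | 423.5 | 50% | 41 |
| 0.8 | 0.61 | 0.631 | 481.6 | 56% | 36 |
| 0.9 | 0.68 | 0.533 | 570.2 | 63% | 31 |

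With 15 homes per arm, power goes from 30% to between 34% (CAC 0.5) and 51% (CAC 0.9).

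**Why the wording of the effect matters.** A raw change score multiplies the variance by 2(1 − r). That is 1.24 at CAC 0.5, worse than ignoring baseline, and 0.63 at CAC 0.9, still worse than adjustment (0.53).

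**The other effect size.** For 30% versus 10%, power exceeds 99% with or without baseline.

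**The case against.** Four points can be made against this, and each limits the finding.

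- A reader might infer that the comparison is undefined, or that a within-arm test is planned. The document does not support that. Section 2.1 sets a two-arm cluster randomised study, section 2.4 sizes it per arm, section 2.6 fixes the ratio, and section 2.8.2 assesses the intervention by intention to treat. Lower than control is the natural reading, and only the abstract's compressed sentence confines the reduction to one arm. The unchanged control share is a planning assumption, not an analysis model.
- A reader might infer that baseline prescribing has been rejected. The covariates are introduced as examples, so baseline is unnamed rather than excluded. A fuller list may stand in the full protocol or the analysis plan. Tables 1 and 2 are not visible and may list baseline data.
- A reader might infer that the best available predictor is being thrown away. Neither part is shown. No before-and-after correlation is given, and a baseline UTI share needs reasons from the homes for earlier prescriptions. Only total prescriptions and DDD could plausibly come from the insurer alone, and even there the window is not stated.
- A reader might take the power figures as evidence of bias or of an underpowered trial. They show neither. A follow-up-only randomised comparison is valid, and the 38% starting point depends on reading the reduction as relative.

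What remains is that the wording and the definition of the main outcome do not match, and that a practical gain in precision is not claimed in the models as described.

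**Conclusion.** The point holds as one of clarity and efficiency, not of validity. The main outcome is called a reduction, is defined as a single-period ratio, and is to be analysed with models that name facility descriptors by way of example and no earlier prescribing. Adjusting the between-arm comparison for each home's own baseline would be better and cheap.

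The size is an illustrative range: power from about 38% to 44–63% with 20 homes per arm, equivalent to needing 31 to 49 homes per arm instead of 57 for 80% power. It rests on 60 prescriptions per home, ICC 0.05, an assumed cluster autocorrelation of 0.5 to 0.9, a UTI-specific baseline and an effect of 30% versus 24%. With only total antibiotic use at baseline the gain would be smaller, by an amount the documents do not allow one to calculate. If the intended effect is 30% versus 10%, the gain is immaterial.

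**What to change.** - State the primary effect as the difference between intervention and control in the UTI share of systemic antibiotic prescriptions during follow-up. Remove from the abstract the phrase that confines the reduction to the interventional group.
- Request from the insurer the 12 months before randomisation for every home, covering prescriptions and DDD.
- In the secondary models, enter the baseline total prescription rate and the baseline DDD respectively, as home-level covariates.
- In the primary model, enter the baseline UTI share if homes can recover the reasons from the registration systems that section 2.2 makes a condition of eligibility. Otherwise enter the baseline total antibiotic rate. Settle which one before outcome data are seen.
- Use baseline as a covariate rather than analysing raw change.

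The cost is one retrospective data extract and one term per model. If the UTI-specific baseline is wanted, the homes must also look up the reasons for a year of earlier prescriptions. Whether the insurer can supply the earlier months should be confirmed first.

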### Cost analysis

2.9

We will carry out a budget impact^[28]^ assessment because the costs are charged to nursing homes. The cost of the intervention will be estimated by considering the time dedicated by trainers and nurses to the intervention and the material resources used to implement and monitor this intervention. Staff time related to this intervention will be estimated from gross salaries and material resources at the purchase price (with depreciation and maintenance if necessary). Costs will be estimated by comparing antibiotics consumption between the 2 groups and valuing them at the purchase price. The budget impact at 3 and 5 years will be estimated with different scenarios of the intervention, and assumptions on the incidence of UTIs in nursing homes.

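### The budget impact treats the nursing home as payer but values staff time from gross salaries, which, read literally, leaves out employer contributions (minor)

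*Protocol article*

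**What the plan says.** Section 2.9 (Cost analysis) gives its reason for a budget impact assessment: "because the costs are charged to nursing homes". It builds the cost of the intervention by "considering the time dedicated by trainers and nurses to the intervention and the material resources used to implement and monitor this intervention". The valuation rule follows: "Staff time related to this intervention will be estimated from gross salaries and material resources at the purchase price", with an allowance for depreciation and upkeep of materials where needed. The antibiotic side is handled separately: "Costs will be estimated by comparing antibiotics consumption between the 2 groups and valuing them at the purchase price". Finally, "The budget impact at 3 and 5 years will be estimated with different scenarios of the intervention", together with assumptions on UTI incidence.

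The section does not define gross salary and does not mention employer contributions. It gives no hours, pay levels, contribution rate or cost shares.

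Sections 2.5.2 and 2.5.3 show whose time is involved. Investigators hold a 30-minute meeting in each home, and the research team visits and telephones: "He will make 1 visit per nursing home every 2 months during the first follow-up period" and "1 member of the research team will call the lead nurses by phone every month". The homes' nurses attend the meeting, do the online self-training and, through the lead nurse, take the calls.

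**The concern.** A budget impact should count what leaves the payer's budget. The stated payer is the nursing home, which employs the nurses whose time is being costed. For an employer, an hour of staff time costs the salary plus the employer's own social contributions. A rule based on gross salary, taken at its word, stops short of that amount, so the stated perspective and the stated unit cost do not match.

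The intervention's labour cost would then be reported too low. Materials and antibiotics are valued at purchase price, which is what a buyer pays, so staff time is the only item whose stated basis, read literally, falls below the payer's outlay. The 3- and 5-year projections would start from a low labour cost if they used the same rule. A reader who uses the result to decide whether homes can afford the programme needs the cost that the homes would actually meet.

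**Working it through.** The cost section contains no numerical result, so there is nothing to reproduce. The check is of the rule itself, and its size can be shown only under assumptions.

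**Inputs from the article (2.9).** The payer is the nursing home; labour is valued from gross salaries; materials and antibiotics are valued at purchase price.

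**Inputs not in the article (assumed).** The employer contribution rate c, as a fraction of gross salary, and the staff share s of the intervention cost when that cost is valued at gross salary.

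**Step 1: staff time.** Let G be the staff cost at gross salary. The employer's cost is G(1 + c), so the rule misses cG. As a share of the employer's cost, the shortfall is cG / [G(1 + c)] = c/(1 + c).

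| Assumed c | c/(1 + c) | Shortfall in staff cost |
|---|---|---|
| 0% | 0/1.00 | 0% |
| 10% | 0.10/1.10 | 9.1% |
| 20% | 0.20/1.20 | 16.7% |
| 30% | 0.30/1.30 | 23.1% |
| 45% | 0.45/1.45 | 31.0% |

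The row c = 0% also covers the case in which the authors meant salary cost with employer charges already included. There is then no shortfall.

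**Step 2: total intervention cost.** Let T be the total at gross-salary valuation, so that staff cost is sT. The total at employer cost is T + c·sT = T(1 + sc), and the shortfall is sc/(1 + sc).

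| Assumed s | c = 10% | c = 45% |
|---|---|---|
| 25% | 0.025/1.025 = 2.4% | 0.1125/1.1125 = 10.1% |
| 50% | 0.050/1.050 = 4.8% | 0.225/1.225 = 18.4% |
| 90% | 0.090/1.090 = 8.3% | 0.405/1.405 = 28.8% |

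These figures show only how strongly the result depends on two unknowns. None of them is an estimate for this trial.

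**Step 3: whose payroll.** Section 2.9 pools trainer and nurse time. The argument from the home's budget applies directly to the home's own nurses. Investigators hold the meeting, and the research team makes the visits and calls; the article does not say that homes pay for this time. Anyone who employs salaried trainers also pays contributions, so gross salary would understate that cost as well, but it is not shown to be a cost to the home.

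**The case against.** The strongest reply is that everything turns on one undefined term in a condensed article. The text says that time will be estimated from gross salaries; it does not say that contributions are excluded, and a full economic plan may define a loaded unit cost. This stands in part: the shortfall is conditional on the ordinary meaning of the term. It does not remove the point, because the article states a valuation rule and goes as far as depreciation and upkeep for materials. If the authors meant loaded cost, the same sentence settles it.

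A reader might also infer three stronger things that the article does not support.

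- *Staff time is the largest recurring cost.* No amounts or shares are given. The intervention also has a website, videos, renewed posters and a competition, and the visits belong to the first 6 months only.
- *The net budget impact is biased towards savings.* Contributions left out would push it that way. But the offset in 2.9 credits only antibiotics and no nurse time saved when fewer are given, which works in the opposite direction. Nurses already in post might also train with no extra outlay by the home, in which case even gross salary could overstate the budget effect. The net direction is open.
- *The error is the same in every scenario.* Section 2.9 does not fix unit costs across scenarios. Even with a fixed unit cost, the effect on the total would change with the staff share.

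**Conclusion.** The concern holds in a limited form. Section 2.9 names the nursing home as payer and values labour on a basis that, in its ordinary meaning, is less than an employer pays. The shortfall in the cost of staff time is c/(1 + c), about 9% to 31% for assumed contribution rates of 10% to 45%, and zero if the term was meant to include employer charges. The size of the effect on total intervention cost cannot be derived from the article, and the sign of the net error in the budget impact cannot be settled from it.

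This is a minor point. It concerns an additional economic analysis and leaves the randomisation, the sample size and the primary and secondary effect estimates untouched. It is still worth correcting, because the rule as written does not match the perspective chosen for it.

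**What to change.** In section 2.9, replace the rule for labour with wording such as: *Staff time will be valued per hour at full employer cost (gross salary plus employer social contributions), by staff category. Time of nurses employed by the nursing home will be reported separately from trainer and research-team time, and the payer of each will be stated. The same unit costs will be used in the base case and in the 3- and 5-year projections.*

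If loaded cost was already intended, the change only makes the term explicit. The cost is a short edit and a revised unit-cost table, with contribution rates taken from a stated source. Reporting by staff category may require the time records to identify who spent the time. No new outcome data are needed. If contributions had been left out, the stated cost of the intervention would rise.
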